### Recruitment, inclusion and exclusion criteria

Recruitment involves an opt-in two-step process for adult motor vehicle crash survivors who have lodged a compensation claim with one of the multisite insurance companies. Insurance companies consisted of one major Compulsory Third Party insurance company in New South Wales and one in Victoria, Australia. Step 1 involves screening by the claimants’ insurance case manager for interest in participating in the research. Step 2 involves the researcher telephoning the potential participant to discuss the research further, followed by emailing information sheets and consent forms to those people who have indicated willingness to participate.

#### Inclusion criteria

Adult (aged 18+) survivors of a motor vehicle crash who have lodged a compensation claim within 3 months of their accidentEnglish speaking

#### Exclusion criteria

Catastrophic or complex injuries such asspinal cord injuryamputationblindnessmultiple fracturesinternal damage requiring extended hospitalizationsevere traumatic brain injury

### Sample size

Based on prior results of CBT and healthy lifestyle interventions [1, 4, 5], the two interventions are assumed to have at least a small to moderate mean effect size of 0.25 (Cohen’s *d*) when compared with the control group. Assuming an α probability of 0.05 and a power of 80 % for a three-group comparison analysis with four measures over time, a sample of 135 participants must be recruited to detect a true difference (see Fig. 1). It is therefore proposed to recruit at least 180 adult participants, randomly assigned to one of the three groups each with at least 60 participants per group. This is to accommodate for the loss to follow-up of approximately 25 % of participants, based on similar research [27].

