**Methods/design:**

This is a randomized, controlled multisite study. Participants include at least 180 adults injured in a motor vehicle crash who have entered a compensation process. Research will compare outcomes in three groups randomly assigned to: one group of 60 adults, who receive a brief email-delivered CBT programme, with one session every 2 weeks for 10 weeks and telephone contact every 2 weeks; a second group of 60 adults, who receive a brief email-delivered lifestyle intervention involving one session every 2 weeks for 10 weeks with telephone contact; and an active waiting-list control group of 60 adults who are provided claims processing-related reading material along with telephone contact every 2 weeks for 10 weeks. Participants will be recruited within 12 weeks of the motor vehicle crash, and will be comprehensively assessed before and after treatment, and 6 and 12 months post-injury. Assuming an *α* probability level of 0.05 and a power of 80 %, at least 180 participants will be recruited. The primary outcome measure is the presence and severity of psychological distress or disorder. Secondary outcome measures include assessment of self-efficacy, resilience employment status, social activity and support, lifestyle and physical health factors, along with process outcome measures of treatment acceptability, feasibility and generalizability.

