### Hypothesis and data analysis

The primary hypotheses assert that brief interventions (CBT and healthy lifestyle) will prevent the development of psychological distress by improving psychological coping skills and healthy behaviours. A further hypothesis is that the intervention groups will show improved resilience and quality of life compared with the control group; however, we are not hypothesizing a significant difference between the treatment groups themselves.

The effectiveness of the interventions will be determined by conducting multivariate analyses of variance with repeated measures for revealing differences within and between groups, as well as reporting effect size changes. Potential confounding factors, such as pre-injury health and education, will be adjusted for in the analysis. Correlation analyses and multiple regression will also be used to analyse predictors of psychological distress over time. The intervention satisfaction questionnaire will be analyzed to assess participant satisfaction of the overall treatment approach. Clinically significant improvements or recovery will be determined by identifying the proportion of participants who demonstrate a significant reduction in their symptoms.

An interim analysis will re-evaluate the assumptions made for the study’s sample size calculation, with re-estimation made if required, unless the trial needs to be stopped as a result of significant and consistent indications of elevated psychological distress associated with the interventions, according to the safety measures and endpoint.

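### The 135 evaluable participants do not give 80 % power at the stated Cohen's d of 0.25 unless an unstated, very high within-person correlation holds

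*Protocol article*

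**What the plan says.** The Sample size section of the protocol article refers to a "small to moderate mean effect size of 0.25 (Cohen’s *d*) when compared with the control group". With alpha 0.05 and 80 % power, it states that for a "three-group comparison analysis with four measures over time, a sample of 135 participants must be recruited to detect a true difference". It then allows for "loss to follow-up of approximately 25 % of participants" and sets the target at 180, "randomly assigned to one of the three groups each with at least 60 participants per group". The Abstract repeats alpha, power and the conclusion that "at least 180 participants will be recruited".

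The text states no within-person correlation, no sidedness, and not whether the powered effect is the group main effect, the group-by-time interaction or a contrast. The section refers to Fig. 1 for the power analysis; that figure is not in the text at hand. The section Hypothesis and data analysis plans repeated-measures multivariate analysis of variance for differences within and between groups, and expects no difference between the two interventions.

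**The concern.** A d of 0.25 is a small difference, and 45 per arm is a small sample for it. Repeated measures can raise power, but only under particular correlations and for particular tests. The effect size is labelled explicitly as Cohen's d against control, so the claim of 80 % power can be tested over the whole plausible range of the missing correlation.

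This is the trial's only power statement. The Background justifies the trial partly by the need for adequate power after several small trials, two of them in compensation claimants with non-significant results. If the claim is wrong by a factor of about two on the d scale, readers have no sound basis for judging what the trial can detect. The sample-size re-evaluation planned for the interim would also begin from an effect size and a sample that do not belong together.

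**Working it through.** **Inputs from the Sample size section:** d = 0.25 for each intervention against control; alpha 0.05; power 80 %; k = 3 groups; m = 4 measures; N = 135 (45 per arm); 25 % loss.

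**Assumptions, because the text does not give them:** within-person correlation rho, equal across all visits and varied; two-sided tests; equal variances.

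**Reproducing the plan's figures.** The inflation is right: 135 / 0.75 = 180. Two standard routes return N = 135 in whole multiples of three:

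- Between-groups repeated-measures F test with 0.25 entered as Cohen's *f* and rho = 0.8: lambda = N·m·f² / (1 + (m − 1)·rho) = 135 × 4 × 0.0625 / 3.4 = 9.93 on 2 and 132 df, power 80.3 %.
- Group-by-time F test with f = 0.125 and rho = 0.4: lambda = N·m·f² / (1 − rho) = 135 × 4 × 0.015625 / 0.6 = 14.06 on 6 and 396 df, power 80.7 %.

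**What these mean on the d scale.** For group means (0, d, d), f = d·√2/3. So f = 0.25 is d = 0.25 × 3/√2 = 0.53. For the interaction, with no baseline difference and a constant difference d at the three later visits, f = d·√(2/9 × 3/16) = 0.204·d. So f = 0.125 is d = 0.61. Neither is 0.25.

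**Power at d = 0.25 with N = 135.** Here f = 0.25 × √2/3 = 0.118 between groups, and 0.204 × 0.25 = 0.051 for the interaction.

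- Between groups: lambda = 135 × 4 × 0.01389 / (1 + 3·rho) = 7.5 / (1 + 3·rho).
- Interaction: lambda = 135 × 4 × 0.002604 / (1 − rho) = 1.406 / (1 − rho).
- Single visit, pairwise: noncentrality 0.25 × √(45/2) = 1.19 on 88 df.
- Baseline-adjusted mean of the three follow-ups: residual variance v = (1 + 2·rho)/3 − rho², which is 0.443 / 0.417 / 0.227 at rho 0.3 / 0.5 / 0.8. Standard error is √(v × 2/45) pairwise, and √(v × (1/45 + 1/90)) with both interventions pooled against control.

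| Test | rho 0.3 | rho 0.5 | rho 0.8 | rho at which power reaches 80 % |
|---|---|---|---|---|
| Between groups, four measures | 40 % | 32 % | 24 % | none ≥ 0 (68 % at rho = 0) |
| Group by time | 14 % | 19 % | 46 % | about 0.90 |
| Single visit, pairwise | 22 % | 22 % | 22 % | not applicable |
| Baseline-adjusted mean, pairwise | 42 % | 44 % | 69 % | about 0.85 |
| Baseline-adjusted mean, interventions pooled | 53 % | 56 % | 81 % | about 0.8 |

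Total N needed for 80 % power at d = 0.25 is 333 / 438 / 594 between groups (177 at rho = 0) and 918 / 657 / 264 for the interaction, at rho 0.3 / 0.5 / 0.8.

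The between-groups row is generous, because it lets the difference of 0.25 exist at baseline too. With equal baselines, as randomization implies, that test has 24 / 19 / 15 %.

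**Size of effect that 135 does detect.** The lambda needed for 80 % power is about 9.86 on 2 and 132 df, and about 13.84 on 6 and 396 df. Between groups, d = √(9.86 × (1 + 3·rho)/120), where 120 = 135 × 4 × 2/9. This gives 0.40 / 0.45 / 0.53 at rho 0.3 / 0.5 / 0.8, again with the difference at all four measures. For the interaction, d = √(13.84 × (1 − rho)/22.5), where 22.5 = 135 × 4 × 2/9 × 3/16. This gives 0.66 / 0.55 / 0.35.

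**The case against.** The strongest defence is that the text leaves rho and the tested effect open, so some analysis may deliver 80 % at d = 0.25. This is partly true. Because the plan expects the two interventions to perform alike, pooling them against control is a natural contrast. Adjusted for baseline, it has 81 % at rho = 0.8. The interaction test gets there at about 0.90. What does not stand is the step from there to the plan's claim: the text invokes no such correlation, and it would have to hold for distress scores from shortly after the crash to 12 months.

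It is also fair to say that Fig. 1 may show the test, the metric and the correlation. A reader might infer that 0.25 was simply an f mislabelled as d. That is the likeliest explanation, but both routes that return 135 depend on a freely chosen rho, so they show what is possible and not what was done.

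A reader might also infer that the interim re-estimation would use the observed difference between arms and so inflate the type I error. The text says only that "An interim analysis will re-evaluate the assumptions made for the" sample-size calculation, with re-estimation if required. It names no such rule, and the provision is partly a safeguard because it allows the assumptions to be corrected.

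**Conclusion.** The concern holds in conditional form. With 45 evaluable per arm and d = 0.25, power falls below 80 % for every test examined at correlations up to just under 0.8. It reaches 80 % only at about 0.8 (pooled, baseline-adjusted), 0.85 (pairwise, baseline-adjusted) or 0.90 (interaction), and at no non-negative correlation for the between-groups test. The sample of 135 matches an effect of about d = 0.53 or 0.61 under the two routes that reproduce it, roughly twice the stated effect.

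A reader might want a single figure for the true power, such as 20 to 45 %. The documents do not support one: across correlations 0.3 to 0.8 the results run from 14 % to 81 %, depending on the test. Nor does it follow that the trial must be enlarged. The error lies in the stated link between 0.25 and 135, not in the inflation to 180. The results assume equal correlation between visits, complete data on 135 participants and, except in the generous between-groups row, no baseline difference.

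**What to change.** Keep the target of 180. In the Sample size section:

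- State whether 0.25 is Cohen's d or Cohen's f. If it is f, give the d against control that it implies (about 0.53 when both interventions differ equally from control).
- Name the effect tested in the power calculation, in line with the planned analysis, and the range of within-person correlations assumed.
- In place of the claim of 80 % power at d = 0.25, give the effect detectable with 80 % power at 45 per arm, and the power at d = 0.25, both for that test and over that range.

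Align the Abstract's sentence on power with the result. The choice of test and correlation belongs to the trial team; the tables above only show how much depends on it.

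The cost is wording and a less favourable stated detectable effect. No extra participants, visits or measurements are needed.

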**Fig. 1 Fig1:**
[figure not shown]
Power analysis

### Type of trial

This study is designed as a multisite, randomized controlled clinical intervention trial.

### Randomization and blinding

Randomization will be determined by the database analyst, who will develop a macro in Microsoft Excel. The macro will be programmed to generate random combinations from six possible permutations (123, 132, 213, 231, 321, 312). Participants will be randomized according to group (for example: 1 = CBT; 2 = lifestyle; 3 = control) based on their entry into the trial and the corresponding permutation. The random group assignment will be kept separately from all online assessments in a pass-coded programme under password security. Participants will not be advised of their randomization, and the database analyst, statistician and study co-ordinator will all be blind to both randomization and group name and number.

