#### Safety measures and endpoint

This study is being conducted by a clinical psychologist highly experienced in the assessment and treatment of mental health disorders, as part of a doctoral study. The occurrence of adverse events, such as severe episodes of anxiety, panic, depression of risk of self-harm during the interventions, are considered safety endpoint measures of this trial. The regular contact by the clinical psychologist will identify whether the safety endpoint measure is required by any participant and appropriate action as per accepted mental health clinical guidelines will be instigated.

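### Fixed blocks of three make one allocation in three certain to anyone who enrols and knows earlier assignments; the database analyst is said both to determine the randomisation and to be blind to it

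*Protocol article*

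**What the plan says.** All places are in the protocol article.

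- **Generation** (Randomization and blinding). "Randomization will be determined by the database analyst, who will develop a macro in Microsoft Excel". The macro will "generate random combinations from six possible permutations (123, 132, 213, 231, 321, 312". Participants are assigned "based on their entry into the trial and the corresponding permutation". No other block size is named.
- **Size** (Sample size). At least 180 participants, "randomly assigned to one of the three groups each with at least 60 participants per group".
- **Blinding** (Randomization and blinding). The article states that "the database analyst, statistician and study co-ordinator will all be blind to both randomization and group name and number". Trial organization, registration and ethical aspects repeats that the database analyst is blind to allocation and gives this as a safeguard of data integrity.
- **Protection of the list** (Randomization and blinding). It is kept apart from the online assessments, under password.
- **Enrolment** (Recruitment, inclusion and exclusion criteria). Insurance case managers screen for interest. Then "Step 2 involves the researcher telephoning the potential participant to discuss the research further", and consent forms follow by email.
- **Delivery** (Interventions, Table 2). The two active arms receive skills modules and calls about practising them. The control arm receives claims reading and calls about that reading.
- **Contact during treatment** (Safety measures and endpoint). One clinical psychologist conducts the study as part of a doctorate. "The regular contact by the clinical psychologist" is the means of detecting adverse events.
- **Timing** (Trial status). Recruitment had begun and was expected to run until July 2017.

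**The concern.** Two separate matters arise in the same section.

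**Predictability.** A block of three holds each arm once. After two assignments in a block are known, the third follows without doubt. The password on the list does not prevent this, because the inference uses past assignments and not the list itself. Past assignments are plain to anyone who sends the modules or makes the calls. Enrolment is a telephone conversation followed by emailed forms, so there is room to influence, even unintentionally, who is pursued and when. The primary outcome is distress measured by self-report scales and diagnostic interviews, so enrolling people by perceived distress would bear directly on the group comparison.

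**Roles.** The article presents the database analyst's blindness as a safeguard. The same section gives that analyst the task of determining the randomisation. As worded, a reader cannot tell whether the safeguard exists.

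**Working it through.** The article gives no predictability figure, so there is none to reproduce.

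**Inputs.** Three arms, 1:1:1; the six listed orderings are all 3! = 6 permutations, so the block size is 3; 180 participants make 180/3 = 60 complete blocks.

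**1. All earlier allocations known.** The best guess is an arm not yet used in the block.
- Place 1: 1/3. Place 2: 1/2. Place 3: 1.
- Average: (1/3 + 1/2 + 1)/3 = 11/18 = 61.1%, or 110 of 180. Chance is 1/3, or 60 of 180.
- Certain: place 3 of each block, 60 of 180 = 33.3%.

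**2. Only half of a shared list seen.** Assumption: each participant falls with probability 1/2 in the part that the guesser sees, and the block boundaries are known.
- Place 1: 1/3 = 4/12.
- Place 2: 1/2 × 1/3 + 1/2 × 1/2 = 5/12.
- Place 3: 1/4 × 1/3 + 1/2 × 1/2 + 1/4 × 1 = 7/12.
- Average: (4 + 5 + 7)/36 = 4/9 = 44.4%.

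**3. Random block sizes 3, 6, 9, equally likely, all earlier allocations known.**
- Guess rates by exact enumeration, sizes known to the guesser: 61.1% (block of 3), 56.1% (6), 53.2% (9). Weighted by block length: (3 × 0.6111 + 6 × 0.5611 + 9 × 0.5319)/18 = 55.5%.
- Sizes withheld (3,000 simulated lists of 180; the guesser knows the three possible sizes but not the size of any block): guess rate 55.3%; certain allocations 3.8%, about 7 of 180.
- If the sizes leak, the expected number of certain places per block is 1 (block of 3), 1 + 1/5 = 1.2 (6) and 1 + 2/8 + (2/8)(1/7) = 1.286 (9). The share is (1 + 1.2 + 1.286)/18 = 19%.

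The average guess rate barely depends on withholding, because guessing the least-used arm needs no knowledge of block size. The gain lies in certainty: 33% falls to about 4%, but only if the sizes stay withheld.

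**4. The analyst's role.** One sentence has the analyst determine the randomisation through a macro that this analyst writes. A later sentence in the same section has the analyst blind to the randomisation, the group name and the group number. Coded arm labels would hide the name only. The wording also claims blindness to the number and to the randomisation itself, so coding does not reconcile the two sentences.

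**The case against.** The strongest reply is that 61% is a conditional worst case. It needs one person who enrols, knows where each block starts and knows every earlier assignment. The article does not say that such a person exists. It does not say that the researcher who phones candidates is the treating psychologist, and the enroller could be the study co-ordinator, who is declared blind. A condensed article may also leave the separation of these roles to the full protocol. This stands, and the size must be stated as conditional. It does not remove the point, because the fixed block of three is stated and is the feature that makes separation of roles essential. Nothing in the article excludes overlap in a doctoral study conducted by one psychologist.

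A reader might infer that over 60% of allocations are predictable. That is not so: 61% is an expected rate of correct guesses and includes the first place in each block, where a correct guess is pure chance. Only one third are certain.

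Some protection exists. Case managers screen first, Table 1 puts consent before randomisation, the list is under password, and baseline measures and adjustment for confounders are planned. These narrow the scope for steering and for bias on measured factors. They do not stop inference from past assignments, and adjustment cannot be relied on for unmeasured factors.

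On the analyst, writing a macro does not require seeing its output. That may be what was meant, but the article says that the analyst determines the randomisation, so the text needs correcting.

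The article names two insurers, "one major Compulsory Third Party insurance company in New South Wales and one in Victoria, Australia", and no stratification. A reader might count that as part of the fault. It is a design preference: separate lists with the same blocks would still give 61% to someone who sees both.

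**Conclusion.** The point holds in two parts.

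First, the stated scheme is permuted blocks of fixed size 3, in order of entry and made public during recruitment. If the enrolling person knows earlier allocations, 60 of 180 are certain and the expected correct-guess rate is 61% against 33%. With half of the list seen, under an assumed even split, the rate is about 44%, still above chance. Whether the condition is met cannot be settled from the article. It does not show that any allocation was foreseen or that selection bias has occurred.

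Second, the account of the database analyst contradicts itself, and this needs no assumption. A reader might conclude that the analyst is in fact unblinded. The article does not establish that; it establishes that the two statements cannot both stand as written.

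**What to change.** 1. For remaining participants, let the macro draw block sizes at random, for example 3, 6 and 9, and withhold the sizes from everyone who recruits. The cost is a small change to the macro and a protocol note. If recruitment stops inside a block of 9, two arms can differ by up to 3, against up to 1 with blocks of 3.
2. Reconcile the analyst's role in Randomization and blinding and in Trial organization, registration and ethical aspects. Either someone outside data handling runs the macro and holds the list, or the database analyst is removed from the blinded roles and the data-integrity statement is amended to match. The second option is a change of text only; the first also needs an independent list holder.

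Stratification by insurer and coded arm labels for the statistician are not needed to resolve this point.

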### Interventions

All participants will be randomly assigned to one of three groups: (i) CBT, (ii) lifestyle or (iii) waiting-list control. For the two treatment groups, participants are delivered fortnightly modules presented in Microsoft PowerPoint presentation with homework worksheets and templates for self-monitoring and practising learnt skills. Emails are brief with two or three paragraphs containing three or four concise sentences as well as a brief case study followed by a weekly summary. At the beginning of every other week, participants are telephoned for a maximum 10 min conversation aimed at (i) encouraging the learning and practising of skills from the previous week, (ii) ‘normalizing’ the challenges of learning new skills, (iii) emphasizing that symptom reduction requires gentle but consistent practice of the skills over time, and (iv) reminding participants about unread materials. The control group is also emailed fortnightly; however, this is restricted to reading information relating to the claims process, and phone calls are aimed at ensuring they are receiving and reading this information. The control group will be offered the programme of their choice, or the programme analyzed as more efficacious after their 6-month follow-up assessment. The contents of each module for each group (original version, March 2015) are presented in Table 2.

**Table 2 Tab2:** Contents of modules for cognitive behaviour therapy, lifestyle and waiting-list control groups

	Cognitive behaviour therapy	Lifestyle	Control
1	Overview	Overview	Reading: ‘A guide for people injured in a motor vehicle crash’
2	Mood and slow breathing skills, self-monitoring	Goal setting and life pacing	Reading: ‘Overview of the claims process’
3	The art of distraction, applying distraction	Self-monitoring and changing unhelpful behaviours	Reading: ‘Obligations of the insurer’
4	Stress and helpful thinking, evidenced-based thinking	Sleep hygiene and sleep self-monitoring	Reading: ‘Obligations of the claimant’
5	Problem solving and conclusions, self-mastery, changeable versus unchangeable problems	Improving well-being through diet and physical exercise, social participation, daily activity schedule	Reading: ‘Finalizing a claim’

